## Methods/design

### Study design

A three-arm, randomized controlled feasibility trial will be conducted in two study sites that include the US (Oklahoma City, Oklahoma, USA) and UK (Greater Glasgow, Scotland, UK). The US site is located at the University of Oklahoma Health Sciences Center (OUHSC) campus within the Tobacco Treatment Research Program that is a part of the Oklahoma Tobacco Research Center. This clinic provides in-person and telephone cessation services to the metropolitan area as well as surrounding towns. The UK site is located at the University of Strathclyde and Stop Smoking Services clinics located in Glasgow and Ayrshire and Arran.

This trial will include a baseline assessment (visit 1), quit date visit that occurs 1 week after the baseline assessment (visit 2), and a third follow-up visit (visit 3) at the end of the 12-week cessation program, or 13 weeks after the baseline visit. The participants will complete 12 total weeks of daily assessments using a smartphone beginning on the quit date (visit 2). The 12-week post-quit follow-up period coincides with the 12 weeks of nicotine replacement therapy (NRT) that participants are eligible to receive as part of their standard smoking cessation services.

### Participant eligibility and recruitment

We aim to recruit 30 current smokers with T2D at each study site (*N* = 60), with 10 in each arm of the study at each location. This sample size is based on our primary feasibility outcomes and sufficient for determining completion of the study protocol and adherence to daily assessments. Eligibility criteria for study enrollment includes adults aged 18 to 75, diagnosed with T2D at least 1 year prior to enrollment, current smoking intensity of at least 5 cigarettes per day, and a self-reported quit attempt in the past 12 months indicating that they had previously been unable to quit. Participants will be excluded from the study if they are unwilling to make a quit attempt through the usual cessation care program or are unwilling or unable to use the smartphone and CO monitor following a brief training session.

Participants will be recruited opportunistically in both the US and the UK through multiple avenues, including T2D clinics using physician referrals and clinic flyers, adult smoking cessation services, diabetes support groups, newspaper and online advertisements, posted and emailed recruitment flyers, posters in health and University settings, recontact of research participants interested in future research, and word of mouth. Interested individuals who meet the inclusion criteria will be given an information pack so they can contact the researcher directly to discuss participation. A follow-up appointment will be made for those who choose to participate where eligibility will be checked and informed consent taken.

In the US, this study will be integrated into the current protocol for standard smoking cessation services at the Oklahoma Tobacco Research Center’s (OTRC) Tobacco Treatment Research Program. Individuals who call directly to the smoking cessation clinic or who are referred to the clinic through electronic medical record referral will be screened for eligibility. Any smoker interested in quitting and eligible for this study will be provided information about the study and the opportunity to participate at their initial smoking cessation appointment.

### Intervention and control groups

Participants will be randomized to one of three groups: (1) a short-term (6 weeks) incentives group, (2) a long-term (12 weeks) incentives group, and (3) a control group with no incentives. Participants in all three study arms will receive the usual smoking cessation care available in each setting. Usual care in both sites will include an in-person or telephone counseling component, selected by the participants, for at least a 6-week period as well as NRT and/or medications for a 12-week period. Due to the limitations of the small feasibility study and the reliance on existing treatment programs for usual care, we will not be able to completely standardize the cessation components in both countries. However, we will explore adjustment for treatment intensity including counseling sessions completed and NRT received during the analysis through multivariable modeling to account for differences in usual care received.

The incentives groups will have the opportunity to earn $20 or £15 per week by providing evidence of smoking abstinence using remote CO monitors. We will validate smoking abstinence via remote biochemical verification through the use of the CoVita iCO™ Smokerlyzer® breath monitor, which is a personal and remote CO sensor that plugs directly into a smartphone [37]. The iCO™ Smokerlyzer® has been demonstrated to be highly reproducible and able to differentiate between smokers and nonsmokers; however, results consistently differ slightly suggesting a need for calibration guidelines [38]. The OTRC has internally evaluated the validity and reliability of the iCO™ Smokerlyzer® integrated into the INSIGHT™ application by testing known concentrations of CO at 5 ppm, 10 ppm, and 20 ppm and found that multiple iCO™ Smokerlyzer® sensors were consistent and accurate enough to differentiate smokers from nonsmokers. Evidence of abstinence each week will be defined as 5 out of 7 days (> 70%) with CO readings of less than 8 parts per million (ppm) submitted through the remote CO sensor. Participants in the short-term incentives program will be eligible to earn weekly incentives for the first 6 weeks of the program, or only during the counseling portion of the usual care program. Participants in the long-term incentives program will be eligible to earn weekly incentives throughout the full duration of the 12-week usual care cessation program, which is the length of time they are eligible to receive NRT as part of usual care. Participants in both incentives groups will be notified weekly about incentives earned throughout the duration of follow-up, and earned incentives for both groups will be distributed in the form of gift cards at the end of the 13 week study (visit 3) following the return of the smartphone. Each weekly incentive is independent and does not require continuous abstinence throughout the entire incentive period. All three groups will be instructed to submit daily assessments for the duration of the 12-week program. Individuals in the control group will be unable to earn incentives and will not be compensated for their participation in the research study due to restrictions of the charity funding source. This is common in the UK and is not anticipated to be a problem. However, participants in the US are often compensated for research. Therefore, individuals in the US control group will be informed that they are eligible to win a tablet computer when they complete the 12-weeks and return the study phone.

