
### Randomization

Participants in this unblinded study will be randomly allocated to one of the three groups based on block randomization. A random number sequence generated by a computer will be created, which will then be used in the randomization feature in Research Electronic Data Capture (REDCap). After an individual provides informed consent at the baseline visit (visit 1), the participant will be asked to return for the quit date at visit 2 1 week later. Prior to visit 2, a study coordinator without prior knowledge of the sequence will randomize the participant via REDCap, allocate the individual to the selected group, and inform the participant of their assigned group at visit 2. Participants will be informed of their assigned group at the second visit in attempt to maximize the likelihood of continuation in the study for individuals who are assigned to the control group and unable to earn incentives. In addition, the control group participants in the US will be reminded of their 1 in 10 chance of winning a tablet after completing the study. Blinding throughout the duration of the study is not feasible because the notification of each weekly earned incentive is part of the intervention.

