### Statistical methods

As this is a feasibility study, we will first examine our primary outcomes by calculating loss to follow-up rates for the follow-up visits and the proportion of daily assessments completed per participant for each study arm. We will also examine monthly recruitment and enrollment rates, and evaluate the acceptability of the program using the exit survey items. Although we are underpowered to test differences, we will explore the feasibility of our study protocol and data completeness by conducting statistical analyses similar to that of a larger trial. We will initially conduct range checks for data values to assess data quality. We will calculate descriptive statistics and compare baseline characteristics between arms to ensure adequate randomization between groups. All questionnaire items will be scored using methodology described in the literature. We will calculate means and standard deviations for continuous measures and frequencies for categorical measures. We will use time-to-event analysis to explore time to relapse and/or time to discontinuing the daily assessments. Smoking cessation assessment data and ecological momentary assessment data will be measured repeatedly and will therefore be correlated within subjects. Thus, our analytic approach will include generalized linear mixed model regression analysis. This analysis approach can handle normal and non-normal outcomes, such as dichotomous smoking status variables, different variance functions, as well as unbalanced designs where the number of repeated observations varies across individuals. Analyses will be conducted using both intention-to-treat and per-protocol approaches. All preliminary results will be interpreted with caution and treated as preliminary due to small numbers in each arm of this feasibility study. For the qualitative components of this study, we will use the transcribed interviews to develop codes and we will use thematic analysis to determine the feasibility and acceptability of this study protocol.

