As this study was developed through a unique multidisciplinary collaboration between investigators in the US and UK, this protocol was designed to account for cultural differences between the two sites. We included subtle differences across sites in regards to recruitment methods, questionnaire items, the cell phone and data plans that will be provided, the amount of incentives that can be earned, and the integration of our study protocol into the local standard cessation services. In designing the protocol, we discovered cultural differences in the expectation of compensation for the participation in research. In the US site, community members are often provided compensation for engaging in research studies, whereas participants in the UK are not routinely offered compensation for research carried out in publicly funded healthcare settings. To account for differences in motivation to participate in research that might pose potential difficulties in recruitment or the engagement of controls in the US, we added a chance to win a tablet for the control group in the US site. Although there is a concern that there might be differential drop out in the control group due to the inability to earn incentives or be compensated for submitting data, this is a feasibility study and this will be evaluated as part of acceptability and feasibility measures. The protocol also included two similar versions of the study assessments that accounted for cultural and language differences, with subtle variations in the response options on survey items, such as race and ethnicity, employment and income.

Overall, this unique international and multidisciplinary protocol will provide an opportunity to examine the feasibility of using mobile technology and financial incentives to increase the success in quitting smoking among a population that faces many critical lifestyle changes that undermine motivation and perceived capability for quitting. With T2D and other chronic conditions on the rise, it is important to explore new ways of addressing smoking cessation for patients with multiple behavior change priorities.

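### Exploratory adjustment for counseling and NRT uptake, which accrue mostly or wholly after allocation, can bias the estimate of the total incentive effect on cessation

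*Protocol article*

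**What the plan says.** The section Intervention and control groups explains that "we will not be able to completely standardize the cessation components in both countries". As the response it states: "we will explore adjustment for treatment intensity including counseling sessions completed and NRT received during the analysis through multivariable modeling". Usual care is described there as counseling "for at least a 6-week period as well as NRT and/or medications for a 12-week period".

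On timing, the Randomization section says: "Prior to visit 2, a study coordinator without prior knowledge of the sequence will randomize the participant via REDCap". Visit 2 is the quit date, and participants learn their group at that visit. The same section calls the study unblinded. Study design places the 12 NRT weeks alongside the 12 weeks after the quit date.

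Statistical methods does not mention this adjustment again. It says: "Analyses will be conducted using both intention-to-treat and per-protocol approaches". Aim 3, under Study aims and hypotheses, seeks a plausible effect size on cessation to help design a large trial.

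**The concern.** The reason for adjusting is a difference between countries, which is fixed before anyone is randomized. The covariates chosen are individual uptake measures that build up during treatment. A participant who is paid for abstinence may attend more sessions or collect more NRT, and one who relapses may stop both. Three problems can follow:

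- If uptake helps people quit, conditioning on it removes the part of the incentive effect that works through uptake.
- If unmeasured motivation drives both uptake and quitting, conditioning on uptake makes the arms differ in motivation at a given uptake level, although randomization had balanced it.
- If abstinence itself sustains attendance, the covariate is partly a consequence of the outcome.

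In each case the coefficient for arm is no longer the total effect of being randomized to incentives. That total effect is what a larger trial would be sized on.

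**Working it through.** **1. Timing.** Allocation takes place before visit 2, and the NRT weeks start at the quit date, so NRT uptake comes wholly after allocation. Counseling is mostly or wholly after it: the short-term incentive period, the first 6 program weeks, is described as the counseling portion of usual care. In the US the study is offered at the first cessation appointment, so some early contact could precede allocation.

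**2. The plan's own figure.** 3 arms × 2 sites × 10 per arm per site = 60, which matches the stated total. With ten per arm planned at each site, country is balanced across arms by design. A country difference in usual care therefore does not confound the arm comparison.

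**3. Size of the bias.** The documents give no inputs, so all of the following are assumptions. Let A be incentives (0/1), U unmeasured motivation (SD 1) and S uptake (SD 1 within arm):

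- S = b·A + c·U + noise
- P(abstinent) = constant + d·A + s·S + g·U

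In a linear model:

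- total effect = d + s·b
- effect adjusted for S = d − g·c·b
- loss = b·(s + g·c)

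The loss is zero when b = 0. If incentives lowered uptake (b < 0), the adjusted effect would be too large.

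| Inputs | b | s | Total | Adjusted | Loss |
|---|---|---|---|---|---|
| Strong: d = 0.10, c = 0.6, g = 0.10 | 0.3 | 0.08 | 0.124 | 0.082 | 34% |
| | 0.5 | 0.08 | 0.140 | 0.070 | 50% |
| | 0.3 | 0 | 0.100 | 0.082 | 18% |
| | 0.5 | 0 | 0.100 | 0.070 | 30% |
| Milder: d = 0.10, c = 0.6, g = 0.05 | 0.3 | 0.04 | 0.112 | 0.091 | 19% |
| | 0.1 | 0.04 | 0.104 | 0.097 | 7% |
| | 0.3 | 0 | 0.100 | 0.091 | 9% |
| | 0.1 | 0 | 0.100 | 0.097 | 3% |

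Simulating the strong set with probabilities confined to 0–1 gives 0.112 against 0.075 (33%) and 0.127 against 0.065 (49%) for s = 0.08. For s = 0 it gives 0.097 against 0.080 (18%) and 0.068 (30%).

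**4. Second mild set, with site in the simulation** (d = 0.15, c = 0.5, g = 0.05, s = 0.05):

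| b | Unadjusted | Site only | Uptake only | Uptake and site |
|---|---|---|---|---|
| 0 | 0.151 | 0.151 | 0.151 | 0.151 |
| 0.25 | 0.163 | 0.163 | 0.146 | 0.145 |
| 0.5 | 0.173 | 0.173 | 0.138 | 0.135 |

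The loss with uptake only is 1 − 0.146/0.163 = 10% and 1 − 0.138/0.173 = 20%. Site adjustment recovers the total effect, but adding site to a model that keeps uptake does not repair it.

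**5. Uptake driven by abstinence.** Suppose arm has no direct effect on uptake, but abstinence raises uptake by k SD. Assume abstinence of 15% and 25%, a true difference of 0.10. The mean within-arm variance of the outcome is v = (0.15×0.85 + 0.25×0.75)/2 = 0.1575, and the adjusted effect is 0.10/(1 + k²v).

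- k = 0.5: 0.10/1.039 = 0.096, a 4% loss
- k = 1: 0.10/1.1575 = 0.086, a 14% loss

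**6. Consequence if such an estimate were used for planning.** Required sample size varies roughly as 1/effect². A 10% loss inflates it by 1/0.90² = 1.23, a 20% loss by 1/0.80² = 1.56, and a 33% loss by 1/0.67² = 2.23.

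**The case against.** The article commits only to exploring the adjustment. It names no outcome or principal model for it, and the statistical section does not repeat it. A reader might infer that the reported incentive effect, and the figure passed on under Aim 3, will be the adjusted one and hence biased. No text ties this model to Aim 3, and no text shows that incentives change uptake. That part of the objection stands.

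The cessation comparison is also acknowledged to be too small to test, and its results are to be treated as preliminary. With assumed rates of 15% and 26% and 20 per arm, the standard error of the difference is √(0.15×0.85/20 + 0.26×0.74/20) = 0.126. Pooling the incentive arms (40 against 20) gives √(0.15×0.85/20 + 0.26×0.74/40) = 0.106. Even the strong inputs with s = 0.08 produce a bias of only about 4 to 6 points (0.112 − 0.075 and 0.127 − 0.065). This limits the practical harm here, but sampling error does not cancel a systematic shift.

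A US/UK indicator will not capture all variation in care: the UK site spans several clinics, and participants choose the counseling mode. This is true, and an explanatory look at uptake is legitimate if labelled as such. Nor is the absence of site from a condensed article an error, since covariate lists are commonly left to the full plan.

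The planned intention-to-treat analysis does not answer the point. It settles who is analysed and in which arm, and a model on that full set that conditions on uptake still does not estimate the total effect.

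**Conclusion.** The point holds in a limited form and is of moderate weight. The document names adjustment covariates that arise mostly or wholly after allocation, for a reason that pre-randomization site would serve better. An incentive effect adjusted for them can be biased for the total randomized effect whenever uptake depends on arm or on abstinence.

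The size is unknown. It is zero without such dependence, about 3% to 20% under mild assumptions, and 33% to 49% under strong ones in which sessions themselves help people quit. All of these inputs are assumed. Nobody should infer that the trial's effect estimate will lose a third to a half of its value: those figures come from the strongest inputs only.

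The primary outcomes, protocol completion and the share of daily assessments completed, are to be reported descriptively and are not affected.

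**What to change.** State in the statistical section, or in the SAP:

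- The Aim 3 effect size on cessation is reported unadjusted, or adjusted only for pre-randomization factors: site (US/UK) and one baseline measure already collected, either the heaviness of smoking index or visit 1 CO.
- Counseling attendance and NRT uptake are reported by arm and site as descriptive feasibility outcomes.
- Any model that includes them is labelled exploratory and mediation-type, and its arm coefficient is not presented as the incentive effect.

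The cost is a sentence or two of text. No new data, visits or participants are needed, and the sample size stays at 60.

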
### Randomization

Participants in this unblinded study will be randomly allocated to one of the three groups based on block randomization. A random number sequence generated by a computer will be created, which will then be used in the randomization feature in Research Electronic Data Capture (REDCap). After an individual provides informed consent at the baseline visit (visit 1), the participant will be asked to return for the quit date at visit 2 1 week later. Prior to visit 2, a study coordinator without prior knowledge of the sequence will randomize the participant via REDCap, allocate the individual to the selected group, and inform the participant of their assigned group at visit 2. Participants will be informed of their assigned group at the second visit in attempt to maximize the likelihood of continuation in the study for individuals who are assigned to the control group and unable to earn incentives. In addition, the control group participants in the US will be reminded of their 1 in 10 chance of winning a tablet after completing the study. Blinding throughout the duration of the study is not feasible because the notification of each weekly earned incentive is part of the intervention.

### Data collection and outcome measures

Assessments of study measures will be obtained at each of the three in-person visits (Week 1, 2, and 13) as well as through a daily assessment using a smartphone that is provided to each participant (Table 1).

**Table 1 Tab1:** Detailed data collection schedule and measurement items

		**Study period**			
		**Enrollment (-t**_**1**_**)**	**Allocation (0)**	**Post-allocation (t**_**1**_**-t**_**12**_**)**	**Close-out (t**_**13**_**)**
	**Assessment items (#)**	**Visit 1 (baseline, week 1)**	**Visit 2 (quit date, week 2)**	**Daily assessment (week 2 to 13)**	**Visit 3 (week 13)**
**Enrollment**					
Eligibility screen		X			
Informed consent		X			
Allocation			X		
**Interventions**					
Short term incentives (6 weeks)		X	X	X	X
Long term incentives (12 weeks)		X	X	X	X
No incentives (control)		X	X	X	X
**Assessments**					
Biological/anthropometric measures	3	X	X		X
Demographic/background information questionnaire	10	X			
Tobacco history questionnaire	17	X			
Heaviness of smoking index	2	X			
Wisconsin smoking withdrawal scale—craving (past week)	4	X			
Self-efficacy scale/confidence	9	X			
Motivation to quit	3	X			
Diabetes questionnaire	5	X			
Diabetes self-management questionnaire	16	X			X
Consideration of future consequences scale	12	X			
Daily stress and anxiety	5			X	
Daily urges to smoke	4			X	
Daily mood and physical symptoms scale	12			X	
Daily self-efficacy/confidence/motivation	4			X	
Daily tobacco and medication use	7			X	
Daily diabetes and health questions	6			X	
Daily CO reading (iCO™ Smokerlyzer®)	1			X	
Study participation exit questionnaire	10				X

#### Assessments at visits 1, 2, and 3

At all three in-person visits that will occur in the treatment clinics, biological/anthropometric measures will be collected by the research coordinator and entered into a secure REDCap database. These measures include height, weight, and tobacco use status measured through expired CO using a Vitalograph Breath CO monitor. At visits 1 and 3, additional measures will be obtained through self-administered surveys in REDCap using a tablet. Participants will complete 10 items related to demographics, which include sex, age, race/ethnicity, marital status, education, employment status, income, and the status of whether the participant lives with a smoker, has an active mobile phone, and if it is a smartphone. We developed a tobacco use history questionnaire that will capture 17 items related to current and past product, dose, and duration of use of tobacco, quit attempt history, perceptions of harm, comorbidities, and medication use. To assess dependence, participants will complete two items from the heaviness of smoking index [39] as well as 4 items from the Wisconsin smoking withdrawal scale for craving [40], both of which have been shown to be valid and reliable. We will use a 9-item self-efficacy scale/confidence to reflect the confidence that they can cope with high-risk situations without relapsing as well as 3 items assessing motivation to quit [41]. In addition to tobacco-related questions, participants will respond to diabetes-related questionnaires, which include a 5-item section related to age of diagnosis, diabetes control, and glycated hemoglobin and a 16-item diabetes self-management questionnaire assessing self-care activities related to diabetes [42]. Finally, we will collect measures of delayed gratification using the 12-item consideration of future consequences scale [43]. Table 1 outlines the assessments and number of items during the in-person visits.

